## 8.1 Protocol Deviations

Major deviations are defined as follows:

- Wrong treatment in contrast to randomization.
- Violation of inclusion and exclusion criteria.
- Missing informed consent.

## 188 8.2 Demographic and Baseline Variables

189 The following variables are considered to be demographic and baseline:

- 190 • Age, sex, height, weight, body mass index.
- 191 • History –Hypertension, Diabetes mellitus, Analgesic medications, Espiratory  
192 diseases
- 193 • ASA
- 194 • NRS
- 195 • Surgical type
- 196 • Duration of surgery, general anesthesia.

197

## 198 9 Efficacy Analyses

199 This analysis adhered to the intention-to-treat (ITT) and per-protocol principle.  
200 Continuous quantitative data were described as mean  $\pm$  standard deviation if  
201 normally distributed, with between-group comparisons performed using  
202 independent t-tests. Non-normally distributed data were summarized as median  
203 (P25, P75) and analyzed using the Wilcoxon rank-sum test. Categorical variables  
204 were expressed as frequencies (percentages), with group comparisons conducted  
205 via Chi-square tests or Fisher's exact test, as appropriate. Ordinal data were  
206 similarly described as frequencies (%) and compared using the rank-sum test.

207 For the primary outcome, intergroup differences were assessed using a generalized  
208 estimating equation (GEE) model implemented via the R package geepack, with an  
209 exchangeable correlation structure. The model incorporated time, group, their  
210 interaction (time  $\times$  group), and adjustments for age, sex, weight, ASA classification,  
211 complications, anesthesia duration, and baseline values. Estimated marginal means  
212 at each time point were visualized using line plots, either as absolute values or  
213 relative changes from baseline.

214 Binary outcomes were reported as counts (%) and analyzed using generalized linear  
215 models to estimate rate differences (RDs) with 95% CI, adjusting for age, sex,  
216 weight, ASA status, complications, and anesthesia duration. For ordinal outcomes,  
217 between-group comparisons employed the rank-sum test, with median differences  
218 and 95% CI calculated. Single-measurement continuous outcomes were analyzed via

219 linear regression, adjusting for the same covariates.

220 Longitudinal outcomes lacking baseline measurements were evaluated using GEE  
221 models (exchangeable correlation) with time, group, their interaction, and  
222 covariates (age, sex, weight, ASA, complications, anesthesia duration). Estimated  
223 trends were plotted by group. All analyses and visualizations were performed in R  
224 (v4.4.1).

225 Results of efficacy analyses will be presented as tables or in text in the final  
226 publication(s), including p-values.

227 9.1 Primary Efficacy Analysis

228 Analysis of primary endpoint (xx) will be performed in accordance with section 9.

229 9.2 Secondary Efficacy Analyses

230 Analyses of secondary endpoints will be performed in accordance with section 9.

231 9.3 Exploratory Efficacy Analyses

232 Further analysis of exploratory analyses will be performed in accordance with  
233 section 9.

234

235 10 Safety Analyses

236 All adverse events which are directly connected to study procedures will be  
237 documented and reported by appropriate statistical methods in accordance with  
238 section 9.

239

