## 5.3 Randomization and Blinding

Potential trial participants were identified by a research team member through electronic medical record screening. Eligible patients were approached, and written informed consent was obtained either before surgery. Patients were randomly allocated in a 1:1 ratio to receive either the intervention group or the control group using Sun Yat–sen University Cancer Center' s (SYSUCC) interactive web–based response system (IWRS). Allocation concealment was ensured by restricting researcher access to the randomization system until study completion. An independent research assistant conducted randomization using sequentially numbered, opaque envelopes containing group assignments. Based on group assignments, the pharmacist prepared identical 5 mL intrathecal solutions (normal saline or morphine) in 10 mL syringes for administration. To ensure blinding, the administering anesthesiologist was excluded from subsequent procedures and data collection. An independent researcher, blinded to group allocation and uninvolved in interventions or analysis, collected all outcome data.

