### 7.3 Covariates and Subgroups

Covariates: Age, Gender, Weight, ASA, Complication, Duration of Anesthesia

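### Anesthesia duration, known only after allocation, is listed as baseline and adjusted for in the primary model and every adjusted secondary model

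*SAP*

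**What the plan says.** Section 7.3 names one covariate set: "Covariates: Age, Gender, Weight, ASA, Complication, Duration of Anesthesia". Section 9 then uses it almost everywhere:

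- Primary outcome: a GEE with time, group and their interaction, adjusted for a list that ends "complications, anesthesia duration, and baseline values".
- Binary outcomes: generalized linear models for rate differences, adjusted for age, sex, "weight, ASA status, complications, and anesthesia duration".
- Continuous outcomes measured once: "linear regression, adjusting for the same covariates".
- Longitudinal outcomes without a baseline value: a GEE with "covariates (age, sex, weight, ASA, complications, anesthesia duration".
- Ordinal outcomes are the exception: "between-group comparisons employed the rank-sum test, with median differences", with no covariates.

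On timing, the schedule in section 5.1 puts both allocation and the intrathecal injection on the day of surgery. Section 5.3 adds, as a blinding measure, that "the administering anesthesiologist was excluded from subsequent procedures and data collection". Section 8.2 nevertheless includes "Duration of surgery, general anesthesia" among the demographic and baseline variables.

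Section 7.2 sets an intention-to-treat analysis of everyone randomized. Section 9 describes t-tests and rank-sum tests in general terms but assigns the primary outcome to the GEE. It names no unadjusted or baseline-only model for that outcome, and no sensitivity analysis.

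**The concern.** A covariate fixed before allocation cannot be altered by treatment, so adjusting for it leaves the target of the comparison intact and usually sharpens it. Anesthesia duration is complete only when anesthesia ends, after allocation and after the study injection, so treatment could alter it. If it does, two problems follow. Any part of the treatment effect that passes through duration is taken out of the estimate. And if duration and recovery share an unmeasured cause, such as surgical difficulty, holding duration fixed makes the arms differ on that cause.

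The SAP does not rule this out. Total intraoperative opioid dosage is a secondary endpoint in section 4.2, so the plan itself treats an effect of assignment on the conduct of anesthesia as an open question. As a continuous outcome measured once, that endpoint would also be adjusted for the duration of the same anesthetic.

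Complications raise a second, separate question. The word has no definition and no time window, so an analyst cannot tell from the SAP which variable to enter in the primary model.

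**Working it through.** **1. The plan's own figure.** Section 6 gives a difference of 6.0, SD 16, α 0.05 (two-sided by section 7.6) and power 80%. The normal formula 2 × (1.960 + 0.842)² × 16² / 6² gives 111.6, so 112 per group. The two-sample t-test gives 112.6, so 113 as stated. With 10% dropout, 113 / 0.9 = 125.6, so 126 per group and 252 in total. The figures reproduce. They rest on an unadjusted comparison of two means and do not depend on this point.

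**2. Condition for bias.** In a linear model, adjusted effect − total effect = −(shift in the covariate caused by assignment) × (within-arm slope of the outcome on the covariate). If either factor is zero, the bias is zero. The SAP gives neither factor, so every input in steps 3 to 5 except the SD of 16 in steps 4 and 5 is an assumption.

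**3. On the minute scale.** Assume, for arm A and unmeasured surgical difficulty U (SD 1):

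- duration = 180 + δA + 40U + 40e₁, so the within-arm SD is √(1600 + 1600) = 56.6 min;
- QoR-15 = 120 + 6A − b(duration − 180) − cU + 14e₂.

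The within-arm slope is −(b + c × 40/3200), so adjusted − total = δ × (b + c × 40/3200). With δ = 10 min:

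| b (points/min) | c (points per SD of U) | Total slope (points/min) | Change in estimate | Share of MICD 6.0 |
|---|---|---|---|---|
| 0.05 | 0 | 0.05 | +0.5 | 8% |
| 0.10 | 0 | 0.10 | +1.0 | 17% |
| 0.05 | 4 | 0.10 | +1.0 | 17% |
| 0.10 | 4 | 0.15 | +1.5 | 25% |

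The signs reverse for δ = −10. Here a longer anesthetic under treatment makes the adjusted estimate too large, and a shorter one makes it too small.

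**4. On a standardized scale.** Size of the change = (shift in SDs) × (within-arm correlation) × 16. For shifts of 0 to 0.5 SD and correlations of 0.1 to 0.4 this runs from 0 to 0.5 × 0.4 × 16 = 3.2 points. A 10 min shift on an SD of 56.6 min is 0.18 SD, towards the lower end of that range.

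**5. Effect on the test.** Simulation, 4,000 runs, 113 per group, linear model at 24 h, treatment lowering the covariate and higher values going with worse recovery:

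| Shift (SD) | Correlation | Adjusted estimate, true effect 6 | Power | Rejection, true effect 0 |
|---|---|---|---|---|
| 0 | 0.3 | 6.0 | 84% | 5% |
| 0.3 | 0.3 | 4.6 | 61% | 10% |
| 0.5 | 0.4 | 2.8 | 28% | 34% |

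The unadjusted analysis had about 80% power and about 5% rejection throughout. The first row shows the harmless case: no shift, no bias and slightly more power. The planned GEE pools several time points and lists no interaction of duration with time, so its shift would depend on a slope averaged over those times. The 24 h model stands in for it.

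**6. Complications, section against section.** Section 8.2 lists hypertension, diabetes and respiratory disease as history, a different word, which leaves room to read complications as perioperative events. But every other covariate in section 7.3 reappears in section 8.2, where history is the natural counterpart, and sections 4.2, 5.1 and 10 call later events adverse events. The text does not settle which is meant.

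**The case against.** The strongest reply is that nothing in the SAP shows or suggests that intrathecal morphine changes anesthesia duration. If it does not, adjustment is unbiased and gains some precision, as the first row in step 5 shows. This stands, and it rules out a stronger reading that a reader might infer: that the primary estimate has ceased to be the effect of assignment and randomization no longer protects it. The documents support only that this may be so.

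The sizes are also assumed, and the top of the minute-scale range is demanding. A total slope of 0.15 implies a within-arm correlation of 0.15 × 56.6 / 16.6 = 0.51 between duration and QoR-15, above the 0.1 to 0.4 used in step 4. Against a standard error of 16 × √(2/113) = 2.13 at the planned size, shifts of 0.5 to 1.5 points are 0.2 to 0.7 standard errors. This stands as a caution on size.

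The raised rejection rates need a zero total effect together with a shifted covariate. That can happen if direct and indirect effects cancel, or if duration and recovery merely share a cause. If the drug affects neither duration nor recovery, the adjusted test keeps its level.

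A reader might also infer that complications certainly arise after randomization, so that the adverse-event models adjust an outcome for an outcome. The SAP does not say so, and comorbidity is a plausible meaning. Section 5.3, for its part, does not time the injection against the start of anesthesia; the schedule in section 5.1 is the better evidence on timing.

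None of this explains why duration is labelled baseline, or supplies a primary model without it.

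**Conclusion.** The point holds for anesthesia duration. It is a post-allocation variable, misfiled as baseline, and it sits in the only model named for the primary outcome and in every adjusted secondary model. The validity of the primary estimate therefore rests on an unstated assumption that assignment leaves duration unchanged. If that is true the bias is nil. If not, its direction follows the sign of the shift and its size cannot be known from the SAP: about 0.5 to 1.5 points either way for a 10 min shift with 0.05 to 0.15 points per minute in total, and up to 3.2 points at the edge of the wider assumed range, against an MICD of 6.0.

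For complications, the defect established is a missing definition and time window. Bias from that covariate arises only on the perioperative reading.

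**What to change.** - Remove anesthesia duration from the primary GEE, the binary models, the linear regressions and the other GEEs. If it is of interest, keep it in a sensitivity analysis labelled as conditioning on a post-allocation variable.
- Replace complications with preoperative comorbidity, defined from section 8.2 as hypertension, diabetes and respiratory disease. Analgesic medications stand under the same history heading but are not a comorbidity and should be left out of the definition.
- Keep age, sex, weight, ASA class and, where measured, the baseline value.
- In section 8.2, move duration of surgery and of anesthesia from the baseline list to intraoperative variables. Align section 7.3 with the revised section 9.
- Surgical type may be added, but only if it is recorded as planned before allocation. Section 8.2 does not say that it is, and the SAP gives no basis for expecting it to replace the prognostic information in duration.

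The cost is SAP wording, with no new data and no change to 113 per group or 252 in total. A small loss of precision is possible: in the harmless scenario of step 5, dropping a covariate correlated 0.3 with the outcome takes power from about 84% to the planned 80%.

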#### Secondary endpoints:

- 1) QoR-15 scores at 48 and 72 h postoperatively,
- 2) cumulative opioid consumption (MME) at 24, 48, and 72 h postoperatively,
- 3) total intraoperative opioid dosage,
- 4) NRS scores during rest or movement in the post-anesthesia care unit (PACU) or at 24, 48, and 72 h postoperatively,
- 5) time to first flatus,
- 6) time to first ambulation,
- 7) supplementary analgesic dosage at 24, 48, and 72 h postoperatively,
- 8) adverse events (dizziness/headache, nausea/vomiting, pruritus, hypotension) at 24, 48, and 72 h postoperatively and
- 9) length of hospital stay.

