| Medical history taking                 | ×                  |                |                 |              |              |              |                         |                                       |
| Allocation                             |                    | ×              |                 |              |              |              |                         |                                       |
| INTERVENTIONS                          |                    |                |                 |              |              |              |                         |                                       |
| Intrathecal morphine or salute         |                    | ×              |                 |              |              |              |                         |                                       |
| Transversus abdominis plane block      |                    | ×              |                 |              |              |              |                         |                                       |
| ASSESSMENTS                            |                    |                |                 |              |              |              |                         |                                       |
| QoR-15 scores                          | ×                  |                |                 | ×            |              | ×            |                         |                                       |
| NRS                                    |                    |                | ×               | ×            |              | ×            |                         |                                       |
| Total opioid consumption               |                    |                |                 | ×            |              | ×            |                         |                                       |
| Time of the first flatus               |                    |                |                 |              | ×            |              |                         |                                       |
| Time of the first ambulation           |                    |                |                 |              | ×            |              |                         |                                       |

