### 7.4 Missing Data

The missing values in Full Analysis Set will not be imputed.

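### Times to first flatus and first ambulation have no end of observation and no censoring rule, so any patient without the event would drop out and the group difference would shrink toward zero

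*SAP*

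**What the plan says.** - Section 4.2 lists "time to first flatus", "time to first ambulation" and "length of hospital stay" as secondary endpoints 5, 6 and 9. Unlike QoR-15, opioid use, pain scores, supplementary analgesics and adverse events, none of the three has a time limit attached.
- Section 9.2 sends all secondary endpoints back to section 9, which names none of these three. The adjusted rule that fits by category reads "Single-measurement continuous outcomes were analyzed via" "linear regression, adjusting for the same covariates". The same section also gives a t-test (normal data) or a Wilcoxon test (non-normal data) for continuous variables and does not say which rule governs. It contains no Kaplan-Meier, log-rank, Cox or competing-risk method.
- Section 7.4 states: "The missing values in Full Analysis Set will not be imputed". Section 7.2 includes all randomized subjects in the final analysis.
- The schedule in section 5.1 has the rows "Time of the first flatus" and "Time of the first ambulation". Each appears with a single mark inside the block for postoperative days 1 to 3 and none in the close-out columns. The table may have been broken when the text was extracted.
- The same schedule has two close-out columns for stay, one for the whole hospital stay and one for the stay after surgery. Both are marked.

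**The concern.** These two outcomes are waiting times. A patient who has not passed flatus or walked when observation ends, or at discharge, has no time to enter in a regression, a t-test or a Wilcoxon test. Without imputation or a censoring rule, that patient is left out. The exclusion is informative, because the patients without a recorded time are mainly the slowest to recover, and removing them cuts off the upper tail in each arm. The slower arm loses more patients, so the two observed means move closer together. If intrathecal morphine delays bowel recovery, the delay would be understated; if it speeds recovery, the gain would be understated. The exclusion would also contradict the intention-to-treat statement in section 7.2.

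Length of stay raises a smaller and different question: which of the two stays in the schedule is the endpoint.

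**Working it through.** **The plan's own figure.** The only sample size in the SAP is for QoR-15 at 24 h (section 6): difference 6.0, SD 16, two-sided 0.05, power 80%.

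- Normal approximation: 2 × (1.96 + 0.84)² × 16² / 6² ≈ 111.6, so 112 per arm.
- t-based solution: 112.6, so 113 per arm, as stated.
- Dropout: 113 / 0.90 = 125.6, so 126 per arm and 252 in total, as stated.

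This reproduces and is not in question. It only supplies the arm sizes used below.

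**Illustration of the loss.** The SAP gives no event times and no share of patients without the event. All inputs here are therefore assumptions: log-normal times with log-SD σ = 0.5, median m, and observation ending at time c.

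- True mean: m × exp(σ²/2) = m × 1.133.
- Share without the event at c: 1 − Φ(z), with z = ln(c/m)/σ.
- Mean among those observed: m × 1.133 × Φ(z − σ)/Φ(z).

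Example with medians 48 and 60 h and c = 72 h:

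- Median 48: z = 0.811, share dropped 21%, observed mean 54.4 × 0.622/0.791 = 42.8 h.
- Median 60: z = 0.365, share dropped 36%, observed mean 68.0 × 0.446/0.642 = 47.2 h.
- True difference 68.0 − 54.4 = 13.6 h; observed difference about 4.5 h.

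| Medians (h) | Observed to (h) | Dropped | True difference (h) | Difference among observed (h) |
|---|---|---|---|---|
| 24 v 30 | 72 | 1% and 4% | 6.8 | 5.3 |
| 30 v 36 | 72 | 4% and 8% | 6.8 | 4.5 |
| 40 v 48 | 72 | 12% and 21% | 9.1 | 4.1 |
| 48 v 60 | 72 | 21% and 36% | 13.6 | 4.5 |
| 48 v 60 | 168 | 1% and 2% | 13.6 | 11.7 |

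**Power**, simulated with 113 per arm. An unadjusted t-test on observed times stands in for the regression.

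- 48 v 60 h, cut at 72 h: about 0.50 for the t-test, against about 0.86 for a log-rank test with censoring and about 0.89 for a rank test that places patients without the event last.
- 24 v 30 h, cut at 72 h: about 0.85, against 0.86 for log-rank. Almost no power is lost, although the estimate is still attenuated.
- 48 v 60 h, observed to 168 h: 0.86, against 0.90 for a rank test that keeps everyone.

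**Second calculation.** This one used 126 per arm, a 72 h window and a median ratio of 0.8 or 1.25, and varied the share of controls without the event. The difference shrinks by:

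- 0 to 1% when practically none lack the event
- 14 to 26% when 2% do
- 25 to 40% when 5% do
- 37 to 52% when 10% do
- 52 to 66% when 20% do

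In every scenario with patients lacking the event, the shift is toward zero.

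**Length of stay.** No arithmetic is needed. Section 4.2 names one stay and the schedule records two. Allocation is marked on the day of surgery and enrolment on the day before, so days before allocation cannot respond to treatment. Under randomization they add noise, not bias.

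**The case against.** A reader might infer that observation stops at 72 h, that patients without the event are coded as missing, and that delayed recovery is therefore certain to be hidden. The SAP supports none of these as fact. No text ends observation of flatus or ambulation at day 3. Section 4.2 attaches 24, 48 and 72 h limits to other endpoints and leaves these two open, which can equally be read as follow-up until the event. The schedule cannot settle it: it shows QoR-15 marks on days 1 and 3 only, although section 4.2 requires a 48 h score, so its cell positions are unreliable. Linear regression is also reached by category, not by name. If every patient has the event while observed, nothing is lost. This objection stands, and it makes the bias conditional. It does not supply the missing rule, and choosing Wilcoxon on the same observed values would not bring the excluded patients back.

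A reader might also extend the censoring argument to length of stay. That does not hold. Every patient discharged alive has a complete stay, the SAP gives no mortality figure, and a mean difference in stay is defensible. Only the ambiguity of definition remains.

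Two cautions about the remedy are fair. Discharge may depend on bowel recovery, so censoring there can be informative. And log-normal times with shifted medians do not have proportional hazards, so a single hazard ratio would be a summary and not an exact description. Both are reasons for a supporting rank analysis, not for keeping the present rule.

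**Conclusion.** The point holds in conditional form. As written, the SAP sends both times to methods that need an observed value, does not impute, and says neither when observation ends nor what happens to a patient without the event. Any such patient would be excluded, contrary to section 7.2, and the group difference would be biased toward zero.

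The size cannot be determined from the SAP. Under the assumed log-normal model it runs from no loss, through slight (5.3 of 6.8 h with 1% and 4% dropped), to severe (about 4.5 of 13.6 h, power about 0.50 against 0.86 to 0.89, with 21% and 36% dropped). The severe case needs a 72 h cut-off that the SAP does not state. With the same medians observed to 168 h, 11.7 of the 13.6 h remains.

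Length of stay needs only a single definition. All three are secondary endpoints, and the QoR-15 result at 24 h is not affected.

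**What to change.** 1. In section 4.2 or 5.4, define both times from the end of surgery and state when observation ends.
2. In section 9, name the two endpoints and keep patients without the event in the analysis as censored. Compare the groups by Kaplan-Meier curves with a log-rank test, or by a covariate-adjusted Cox model, and say which one governs.
3. Because discharge may depend on bowel recovery, add a sensitivity rank analysis that places patients without the event last.
4. Report the number without the event in each arm, so that the reader can judge how much the handling matters.
5. Specify the length-of-stay endpoint as postoperative stay, and report total stay descriptively.

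The cost is SAP wording and standard code, with no change to the sample size. The downside is that a hazard ratio and medians replace an adjusted mean difference in hours, which some readers find easier to interpret.

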### Exclusion criteria:

Patients will be excluded if they had:(1) declined surgery due to unforeseen circumstances or personal preference preoperatively, (2) had neurological dysfunction, (3) had contraindications to lumbar puncture, (4) had a history of preoperative opioid use, (5) reported baseline pain (assessed via the numerical rating scale [NRS]) with a score  $>3$ , or (6) required conversion to open surgery or secondary operation.

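### The plan records a preoperative pain NRS, but no analysis written for a secondary outcome adjusts the repeated NRS endpoint for it

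*SAP*

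**What the plan says.** Secondary endpoint 4 in section 4.2 is "NRS scores during rest or movement in the post-anesthesia care unit (PACU) or at 24, 48, and 72 h postoperatively", so pain is a repeated outcome.

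A preoperative pain score exists. Section 5.2 excludes patients who "reported baseline pain (assessed via the numerical rating scale [NRS]) with a score" above 3, so everyone who is eligible enters with a score of 0 to 3. Section 8.2 opens its list with "The following variables are considered to be demographic and baseline", and NRS is one of the items.

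Section 9 describes two GEE models with an exchangeable correlation structure. The first is introduced by "For the primary outcome, intergroup differences were assessed using a generalized" estimating equation, and its adjustment set ends with "complications, anesthesia duration, and baseline values". The second rule begins "Longitudinal outcomes lacking baseline measurements were evaluated using GEE" and adjusts for "covariates (age, sex, weight, ASA, complications, anesthesia duration). Estimated", with no baseline term. Ordinal outcomes are compared by a rank-sum test without covariates. Section 9.2 sends all secondary endpoints back to section 9, and the covariate list in section 7.3 does not include the preoperative NRS.

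In Fig. 2 the QoR-15 row is marked on the day before surgery. The NRS row starts at the PACU.

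**The concern.** Section 9 has a rule for the primary outcome and a rule for repeated outcomes without a baseline. It has none for a repeated secondary outcome that does have a baseline, and NRS is such an outcome. The analyst must therefore choose. One option is the second GEE, which ignores the preoperative score. Another is the rank-sum route, which ignores every covariate. The third is to extend the QoR-15 model to NRS, which the plan does not say to do. These options differ in the summary they estimate (a mean or a median difference), in their covariates and in their p-values. A SAP is meant to settle that choice before the data are seen.

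At stake are some precision and the correction of any chance imbalance in preoperative pain, for a pain endpoint in an analgesia trial. The value needed is one the trial must obtain anyway to decide eligibility.

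**Working it through.** **Which routes use the preoperative score**

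| Route in section 9 | Written for | Uses a baseline value? |
|---|---|---|
| GEE, time × group, covariates and baseline | Primary outcome (QoR-15) | Yes |
| GEE, time × group, covariates | Repeated outcomes without a baseline | No |
| Rank-sum test | Ordinal outcomes | No, and no other covariate |

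The first model includes time and reports marginal means at each time point, so it in effect also covers QoR-15 at 48 and 72 h. Baseline adjustment is thus written for QoR-15 and for no other endpoint.

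**The plan's own figure.** Section 6 gives 113 per group and 252 in total for QoR-15 (difference 6.0, SD 16, two-sided α 0.05, power 80%).
- Normal approximation: n = 2 × (1.960 + 0.842)² × (16/6)² ≈ 111.6, so 112.
- Two-sample t-test: 112.6, so 113, as stated.
- Dropout: 113 / 0.90 = 125.6, so 126 per group and 252 in total, as stated.

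The figures reproduce, and this point does not dispute them. The 113 per group is used below only as the number available for the NRS comparison.

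**What adjustment would gain.** Let ρ be the correlation between preoperative and postoperative NRS. The SAP does not give it, so a range is assumed. At one time point:
- residual variance falls by ρ²;
- the equivalent gain in patients is 1/(1 − ρ²) − 1;
- the confidence interval narrows by the factor √(1 − ρ²);
- an effect with 80% power unadjusted, at 113 per group, has power Φ(2.802/√(1 − ρ²) − 1.960) after adjustment.

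| Assumed ρ | Variance removed | Equivalent extra patients | CI width factor | Power |
|---|---|---|---|---|
| 0.1 | 1% | 1.0% | 0.995 | 80.4% |
| 0.2 | 4% | 4.2% | 0.980 | 81.6% |
| 0.3 | 9% | 9.9% | 0.954 | 83.6% |

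**Effect of the entry cap.** Restricting baseline NRS to 0–3 narrows its spread and lowers ρ. If the cap reduces the baseline SD to a fraction u of its uncapped value, an uncapped correlation R becomes R·u / √(1 − R² + R²u²). With u assumed between 0.4 and 0.8:
- R = 0.3: from 0.12/√(0.91 + 0.0144) = 0.125 to 0.24/√(0.91 + 0.0576) = 0.244.
- R = 0.5: from 0.20/√(0.75 + 0.04) = 0.225 to 0.40/√(0.75 + 0.16) = 0.419.

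Unless the uncapped correlation is strong, the realistic gain is therefore in the lower part of the table.

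**The case against.** The best reply is that section 9 keeps the second GEE for outcomes without a baseline, so by implication an outcome with a baseline takes the first. On that reading NRS is already adjusted. The inference is sensible, but it is written nowhere: the first model is introduced for the primary outcome alone, and section 7.3 does not supply the missing covariate. The reply does show that one cannot claim the plan has assigned NRS to the model without a baseline. The plan has not assigned it at all.

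A second reply is that the endpoint is split into rest and movement, while the documented preoperative score is a single one of unspecified type. Treating movement pain as lacking a matched baseline is then defensible. This stands as a limit on the fix. It does not prevent the single score from serving as a covariate in both models.

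Third, a reader might infer from Fig. 2 that the schedule contradicts the entry criterion and that the score would go unrecorded. The documents do not support this. The eligibility screen is marked on the day before surgery and can include the score, and section 8.2 expects NRS to be summarised at baseline. What remains is an inconsistency of presentation between the NRS row and sections 5.2 and 8.2.

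Fourth, the gain is small and rests on assumed correlations. That is correct. The calculation also treats one time point and ignores the six covariates already in the GEE, so the partial correlation that matters may differ.

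**Conclusion.** The point holds as a gap in specification with a modest cost in precision. A preoperative NRS is required and is listed as a baseline variable, and no route written for a secondary outcome uses it. On assumed correlations of 0.1 to 0.3, between about 1% and 9% of residual variance is left on the table, with the lower end likelier because of the cap at 3.

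A reader might go further and infer that the NRS comparison is biased. It is not: randomisation keeps the unadjusted contrast unbiased, and leaving the baseline out costs only precision and correction of chance imbalance. Nor do the documents rank NRS above the other eight secondary endpoints. No stated figure changes. Severity is low.

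**What to change.** Add to section 9 that NRS at rest and NRS on movement are each analysed with the time × group GEE, using the covariates already listed plus the single recorded preoperative NRS (0–3). State whether that score was taken at rest or on movement. If it is of one type only, say that the same score enters both models.

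In Fig. 2, add a mark for NRS on the day before surgery, to agree with sections 5.2 and 8.2. Section 7.4 rules out imputation, so a patient without a recorded preoperative score would drop out of the adjusted model. The mark makes that less likely.

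The cost is a sentence or two and one mark in a table. No new measurement is needed, and the sample size is unaffected.
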